### Sample size estimation

In the past years, approximately 1300 patients with a relevant diagnosis were admitted at the stroke unit of our hospital annually. Of these patients, 60% had an ischemic stroke, 32% had a transient ischemic attack, and 8% were admitted with intracerebral hemorrhage. With an expected dropout of approximately 25%, we aim to include *n* = 1040 patients (Fig. 1). This number allows for exploratory descriptive and inferential analyses with high precision and power, including subgroup analyses and the use of multivariate and longitudinal models. While the planned analyses are of exploratory nature, sample size calculations, done with GPower [7] show that in order to identify a small effect (H0 ρ^2^ = 0.01 and H1 ρ^2^ = 0.05 in a two-sided test with a power of 0.90, a regression analysis with 25 predictors the analysis of data of 846 cases are necessary, which is below the expected sample size.

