Research questions 2 and 3: The data will be analysed by descriptive and inferential statistics, Depending on the outcome, (generalised) multilevel linear (patient-reported global health) and logistic (mental and motor health) regression analyses will be conducted. Factors that are believed to possibly influence the outcomes will be integrated in form of covariates. These will comprise demographics, pre-existing deficits and prior strokes, and deficits at admission (NIHSS) since recent studies have shown a negative influence of impaired motor function on different PROMIS domains(Katzan, Thompson, et al., 2018). Additionally, survival analyses (mortality) will be performed. Exploratory structural equation models are fitted to identify differential characteristic patterns of the outcomes. Further, exploratory subgroup analyses are planned, using regression models that fit the respective research questions. Results with *p* < .05 will be considered as statistically significant. As this study is of explorative nature, no adjustments for multiple testing will be made. However, the elevated risk of an occurrence of type-I errors will be regarded at the interpretation of the results. Missing values will be accounted for by using mixed modelling techniques. Sensitivity analyses will be performed when no mixed models are used. The influence of the NIHSS on the outcomes will be analysed separately using median and nonparametric tests.

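### NIHSS is tested separately with no stated adjustment and diagnosis is not a named covariate, so a TIA-versus-stroke difference can be read as an effect of NIHSS

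*Protocol article*

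**What the plan says.** All of this stands in the protocol article.

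- **Covariates** (Data analysis and management). The general rule is open: "Factors that are believed to possibly influence the outcomes will be integrated in form of covariates". A list follows: "These will comprise demographics, pre-existing deficits and prior strokes, and deficits at admission (NIHSS". Diagnosis is not on it.
- **Separate NIHSS analysis** (same section): "The influence of the NIHSS on the outcomes will be analysed separately using median and nonparametric tests". Nothing is said about adjustment, stratification, the handling of the two follow-up times, or how the result relates to the NIHSS coefficient in the regressions.
- **Subgroups** (same section): "Further, exploratory subgroup analyses are planned, using regression models that fit the respective research questions". The subgroups are not named.
- **Case mix** (Sample size estimation): "Of these patients, 60% had an ischemic stroke, 32% had a transient ischemic attack, and 8% were admitted with intracerebral hemorrhage". All three diagnoses are eligible under Inclusion/exclusion criteria.
- **Aim** (Aim of the trial): the study asks which medical and patient-related factors influence treatment outcome.

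**The concern.** Diagnosis is settled by the index event and comes before the NIHSS score. It plausibly affects both that score and later health-related quality of life. An association between NIHSS and outcome that ignores diagnosis therefore mixes two contrasts: more against less severe deficit among patients of the same type, and TIA against completed stroke. With about a third of patients in the TIA group, the second contrast can carry much of the crude result.

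A standard median or rank test also drops the covariates that the plan itself considers relevant, and it lies outside the mixed models on which the plan relies for missing values. The same predictor is assessed twice at the 0.05 level, with no statement of which result answers the question about influence. At stake is the objective of identifying factors behind outcome: a reader could take a significant crude test as evidence on severity when part or all of it is case mix.

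**Working it through.** **1. What the documents fix.** The diagnosis mix is 60/32/8%. Planned inclusion and loss: "With an expected dropout of approximately 25%, we aim to include *n* = 1040 patients". If the loss is taken after inclusion, 1040 × 0.75 = 780 patients are analysed, made up of 780 × 0.60 = 468 ischemic stroke, 780 × 0.32 ≈ 250 TIA and 780 × 0.08 ≈ 62 hemorrhage. The plan states no figure for the NIHSS analysis, so there is none to reproduce.

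**2. What must be assumed.** The documents give no NIHSS distribution, PROMIS-10 mean or residual SD by diagnosis. Everything below is an illustration on assumed inputs.

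**3. Mechanism by arithmetic.** Suppose NIHSS has no effect within diagnosis and TIA patients score d T-points higher. The slope of outcome on NIHSS that leaves out diagnosis is

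slope = d × cov(TIA, NIHSS) / var(NIHSS).

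Assume mean NIHSS of 0.5 in TIA (Poisson, variance 0.5) and 5 in the others (negative binomial, shape 1.5, variance 5 + 25/1.5 = 21.67).

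- cov = 0.32 × 0.68 × (0.5 − 5) = −0.979
- var = 0.32 × 0.5 + 0.68 × 21.67 + 0.32 × 0.68 × 4.5² = 0.16 + 14.73 + 4.41 = 19.30
- slope = −0.979 / 19.30 × d = −0.0507 × d

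For d = 2, 3 and 5 this gives −0.10, −0.15 and −0.25 T-points per NIHSS point, where the true within-diagnosis slope is zero.

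**4. How often a crude test would be significant.** Simulation on the inputs of step 3, residual SD 10, n = 780, 300 cohorts per row:

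| TIA advantage (T-points) | Mean Spearman correlation | Crude test significant | Crude slope | Slope with diagnosis |
|---|---|---|---|---|
| 2 | −0.06 | 34% | −0.10 | about 0 |
| 3 | −0.09 | 66% | −0.16 | about 0 |
| 5 | −0.14 | 97% | −0.25 | about 0 |

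A second set of assumptions used mean NIHSS of 1, 5 and 8 in TIA, ischemic stroke and hemorrhage, SD 9, and NIHSS split at its median. The split is an assumption, since the article does not describe one. With 2000 cohorts per row:

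| TIA advantage (T-points) | Rank test | Median test | Regression with diagnosis |
|---|---|---|---|
| 2 | 29% | 21% | 5% |
| 3 | 55% | 40% | 5% |
| 4 | 81% | 64% | 5% |
| 5 | 94% | 82% | 5% |

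The spread assumed for NIHSS matters somewhat. With two other choices the rank test ranges over 28–91% or 35–96%, and the median test over 17–75% or 23–86%.

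**5. The regression without diagnosis.** In the same kind of simulation, a linear regression on NIHSS alone is significant in 18–77% or 29–91% of cohorts, depending on the assumed spread. It has no other covariates; those in the plan might absorb part of this.

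**6. If NIHSS has a real effect.** With a true slope of −0.5 and the inputs of step 3, the crude slope is −0.60, −0.66 and −0.76 for TIA advantages of 2, 3 and 5. With diagnosis in the model it is about −0.50. The crude test is then rightly significant, but the crude slope is too steep by 0.10 to 0.26.

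**The case against.** The strongest reply is that a condensed article is being read as if it were complete. The covariate rule is open, the sample size section speaks of 25 predictors, and regression-based subgroup analyses are planned that could be by diagnosis. The full list may stand in a document not shown. This is fair, and it is why the point about the regressions is conditional on the list being complete. It does not reach the separate test, for which the article does name a method: neither an open covariate rule nor unnamed subgroups would adjust it.

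A second reply is that a nonparametric look at a skewed ordinal score beside an adjusted model is ordinary practice, and that crude and adjusted results answer different questions. That stands. A reader might infer that the unadjusted test is the only NIHSS analysis, or that the two results will conflict. The documents support neither: NIHSS is also in the multivariable models, and no conflict is shown. Nor does the article say that NIHSS will be dichotomised or that only p-values will be reported.

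A third reply is that part of the article frames the objective as prediction, for which confounding is not the criterion, and that NIHSS may be partly the route by which diagnosis acts. The wording is indeed mixed, but the aim and the analysis sentence both speak of influence. The mediation point does not remove the problem, because diagnosis precedes NIHSS and can still confound its association with outcome.

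Finally, the rejection rates assume no NIHSS effect within diagnosis, whereas the plan itself cites evidence that impaired motor function worsens PROMIS domains. This also stands: if the effect is real, those rates are not false-positive rates, and step 6 is the relevant case.

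**Conclusion.** The concern holds in a limited form. NIHSS is assessed twice, the separate assessment has no stated adjustment, and diagnosis is not a named covariate in a cohort with about 32% TIA. The separate test, and the regression if its list is complete, can therefore attribute a diagnosis difference to NIHSS.

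A reader might go further and conclude that the NIHSS result is confounded, or that a third to nearly all significant findings would be false. The documents support neither statement, because they hold no data on NIHSS or outcome by diagnosis. The range of roughly 30% to 95% for a crude rank test, against about 5% with diagnosis in the model, rests on 780 analysed patients, the assumed NIHSS distributions and SDs, a TIA advantage of 2 to 5 T-points and a zero within-diagnosis effect. It shows that the problem can be material, not how large it will be.

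The study is exploratory and its other analyses do not depend on this test. The change is still worth making, because it improves the answer to a stated objective at almost no cost.

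**What to change.** In Data analysis and management:

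1. Name diagnosis (ischemic stroke, TIA, hemorrhage) as a covariate in all outcome models.
2. State that inference on the influence of NIHSS comes from the adjusted mixed model.
3. Label the separate median and nonparametric tests as crude and descriptive, or stratify them by diagnosis.

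The cost is one sentence and two degrees of freedom (three diagnosis groups). Diagnosis and NIHSS are already collected. A log or spline form for NIHSS, and NIHSS-by-time or NIHSS-by-diagnosis terms, are optional refinements and not needed to resolve this point.

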#### Software

The electronic health record will be used for data collection and storage. For preparation and most quantitative data analyses, it is anticipated to use the software R (https://www.r-project.org) and IBM SPSS Statistics (https://www.ibm.com/analytics/spss-statistics-software). Lastly, the software MAXQDA (https://www.maxqda.com) will be used for qualitative data analyses.

#### Perspective

Our study protocol represents the first prospective cohort study using the ICHOM Standard Set for Stroke to assess PROMs in stroke patients. Through open inclusion criteria, we attempt to gather a broad spectrum of stroke patients that is representative for the population of acute stroke patients treated on stroke unit in daily routine care in a German metropolitan regions. Information gathered from the process evaluation will help to understand the facilitators and barriers of the standard use of PROMs –also in the long term- in the routine stroke care. The analysis will show, what might have to be adjusted for a smooth and successful implementation and realization of an extended and long-term treatment assessment. Should the analysis show that such an implementation is feasible and accepted amongst affected persons, measures will be taken that the implemented enquiry remains in use within the routine health care at the stroke unit of the University Medical Centre Hamburg-Eppendorf after the end of the trial. Furthermore, the results of the process evaluation will help to accomplish and accelerate the implementation of such enquiries in other settings. Information analyzed from follow up assessments should describe health-related difficulties in everyday life and might show predictive patient or therapy-related factors concerning different groups of patients. Our analysis will help in identifying subgroups of stroke patients with increased risk of impaired quality of life after stroke that may be targeted by specific interventions. Overall, the information collected in our study will help to bring the patients’ perspective into the focus of stroke care and may inform future strategies for improving stroke treatment at different levels.

## Data Availability

The data will be deposited in a protected server of the University Medical Centre Hamburg-Eppendorf. Access is strongly regulated even for study personnel. Owing to the difficulty of de-identification (routine care, qualitative data, etc.), individual participant data will not be shared publicly. Upon reasonable request that includes a methodologically sound proposal for the usage of data that is also approved by the responsible review committee data may be shared.

## Abbreviations

AIS: Acute ischemic stroke
EHR: Electronic health record
ICD-10: International Statistical Classification of Diseases and Related Health Problems 10th revision
ICH: Intracerebral hemorrhage
ICHOM: The International Consortium for Health Outcomes Measurements
ICHOM-SSS: The International Consortium for Health Outcomes Measurements -Standard Set for Stroke
PHQ-4: Patient Health Questionnaire-4
PROMIS-10: Patient-reported Outcomes Measurement Information System 10-Question Short Form
PROMs: Patient-reported Outcome measures
smRSq: simplified modified Ranking Scale questionnaire
TIA: Transient ischemic attack
